#### Implementation Climate

We will measure implementation climate using the Implementation Climate Scale [41], an 18-item rating scale that measures employees’ shared perceptions of the policies, practices, procedures, and behaviors that are expected, rewarded, and supported in order to facilitate effective EBI implementation. The Implementation Climate Scale is a psychometrically validated and reliable instrument (α = 0.81–0.91). We will explore implementation climate as a potential mediation variable.

#### *Team collaboration intensity*

At baseline, exit and sustainment, we will measure the density of connections among people identified on the ranked list for each site for both treatment and control. For each site, we will calculate the number of reported EBI collaboration ties divided by the number of possible EBI collaboration ties [39].

#### *Implementation reach*

At exit and sustainment on the social network survey, we ask each person to identify people from the roster that they collaborated with during the past year to support the EBI being implemented at their site. We will measure implementation reach for treatment and control sites by calculating the number of reported EBI collaboration ties divided by the number of people on the roster.

### Child and family outcomes

We will collect data on several secondary outcomes, including child and family outcome data specific to each intervention, reach and acceptability of the intervention.

### MTG. Family Empowerment

We will use the Family Empowerment Scale [42], a 34-item measure that measures empowerment in families with children who have emotional, behavioral, or developmental disorders. The Family Empowerment Scale has three subscales: Family, Service System, and Social Politics. Higher scores are indicative of higher family empowerment.

### RR. Peer Engagement

The Clinical Global Impression [43] is a 7-point scale designed to measure overall severity in the child’s peer engagement from baseline. Improvement scores at end of intervention range from 1 (Very Much Improved) to 4 (Unchanged) to 7 (Very Much Worse).

### SDLMI*.* Self-Determination

We will use the Self-Determination Inventory: Student Report [36], a standardized measure of self-determination that includes 21 items developed to document change in the self-determination of adolescents aged 13 to 22. The assessment is completed online. The Self-Determination Inventory: Student Report was validated with over 4,500 youth with and without disabilities, including ASD.

### Data analysis

We will analyze effectiveness of the UNITED implementation strategy with each intervention by using a generalized linear mixed model to compare outcomes (primary: MTG/RR/SDLMI fidelity; secondary: MTG = Family Empowerment; RR = CGI; SDLMI = student report) between UNITED and IAU from baseline to end of intervention stage.

Power calculation: Sample size for each study was determined based on statistical power to detect a difference in primary outcome (EBI implementation fidelity) contrast, a between group (UNITED vs IAU) mean comparison in change in fidelity from baseline to the end of intervention phase (assuming 80% power, a Type I error rate of 5%, a within-person correlation in implementation fidelity of *r* = 0.36 – based on preliminary data from each intervention, estimated attrition rate of 20% for MTG and 30% for RR and SDLMI, and variance inflation factor (nesting of providers within schools/agencies) of 1.4 (RR) to 1.6 (MTG & SDLMI). For MTG a difference of 15% in fidelity corresponds to a moderate standardized effect size of d = 0.48 in between strategies change in peer navigator fidelity (based on previous data, sd = 31). For RR a difference of 0.2 corresponds to a moderately large standardized effect size of d = 0.7 in between groups change in paraprofessional fidelity (based on previous data, sd = 0.28). This is a minimally clinically significant difference in change: differences less than 0.2 fidelity amount to differences of less than 2 RR strategies in a 10-min unstructured play time. For SDLMI a difference of 15% in fidelity corresponds to a moderately large standardized effect size of d = 0.79 in between strategies change in paraeducator fidelity (based on previous data, sd = 18.77).

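### The RR and SDLMI provider numbers fit a baseline-adjusted comparison, but the stated contrast is change from baseline, for which power is about 64-65% or 73-78%, depending on what the SDs are

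*Protocol article*

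**What the plan says.** The Data analysis section of the protocol article sizes each study on "a between group (UNITED vs IAU) mean comparison in change in fidelity from baseline to the end of intervention phase". Its inputs are:

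- Error rates: "assuming 80% power, a Type I error rate of 5" per cent. Sidedness is not stated.
- Correlation: "a within-person correlation in implementation fidelity of *r* = 0.36".
- Attrition: "estimated attrition rate of 20% for MTG and 30% for RR and SDLMI".
- Clustering: "variance inflation factor (nesting of providers within schools/agencies) of 1.4 (RR) to 1.6 (MTG & SDLMI").
- Effects: "For RR a difference of 0.2 corresponds to a moderately large standardized effect size of d = 0.7", with an SD of 0.28. For SDLMI, a difference of 15 points with an SD of 18.77, given as d = 0.79.

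The section describes each d as an effect in between-group change. It does not say whether the SDs are of change or of a score at one time point, and it prints no variance formula.

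The planned model is a generalized linear mixed model comparing outcomes "between UNITED and IAU from baseline to end of intervention stage". How baseline enters that model is not given.

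The Participants section and Table 1 give 56 RR and 53 SDLMI school personnel per arm. For MTG they give 24 peer navigators and 120 families per arm.

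**The concern.** A correlation between baseline and end fidelity can enter a sample size in two ways. Adjusting the end score for baseline multiplies the variance by 1 - r². Subtracting baseline multiplies it by 2(1 - r) when the two SDs are equal. At r = 0.36 these factors are 0.87 and 1.28, so one reduces the required number and the other raises it. With equal SDs and r below 0.5, subtracting baseline is less efficient than ignoring it.

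The text names the second contrast, while the numbers fit the first. Fidelity is the primary outcome. If the analysis follows the wording, the chance of missing the targeted effect in RR or SDLMI is larger than the 20% the plan accepts.

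**Working it through.** **Inputs.** From Data analysis: r = 0.36; RR d = 0.2/0.28 = 0.714, variance inflation (VIF) 1.4, attrition 0.30; SDLMI d = 15/18.77 = 0.799, VIF 1.6, attrition 0.30. From Participants and Table 1: 56 and 53 providers per arm. Assumed: two-sided 5% test, two-sample noncentral t, equal arms.

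**Step 1: reproduce the planned sizes.** Find the smallest whole n per arm giving 80% power at effect d/√v, where v is the variance factor. Then N = n × VIF/(1 - attrition).

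| Variance factor v | RR | SDLMI |
|---|---|---|
| 1 - r² = 0.8704 | 28 × 1.4/0.7 = **56.0** | 23 × 1.6/0.7 = **52.6** (53) |
| 1 (r unused) | 32 × 1.4/0.7 = 64.0 | 26 × 1.6/0.7 = 59.4 |
| 2(1 - r) = 1.28 | 41 × 1.4/0.7 = 82.0 | 33 × 1.6/0.7 = 75.4 |

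Only the first row matches under this recipe. With d = 15/31 = 0.484, VIF 1.6 and attrition 0.20, the first row also gives 60 × 1.6/0.8 = 120 for MTG. That figure is the number of families per arm, whereas the MTG effect is stated for peer navigator fidelity and there are 24 navigators per arm. The match helps identify the formula. It does not show that MTG is adequately sized.

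The formula is inferred, and other routes come close. Taking v = 1 with the normal approximation, and inflating by (1 + attrition) instead of dividing by (1 - attrition), gives 56.0 for RR and 51.1 for SDLMI (up to 54.4 across variants). That route leaves r unused, handles attrition incorrectly and gives 129-134 for MTG. A one-sided change calculation with the same attrition step gives 56.5 and 51.5, but about 130 for MTG. The 1 - r² route is the best explanation, not the only possible one.

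**Step 2: power at the planned sizes.** Effective n per arm = N × (1 - attrition)/VIF. RR: 56 × 0.7/1.4 = 28.0. SDLMI: 53 × 0.7/1.6 = 23.2. The ranges cover rounded and unrounded d, and t and normal calculations.

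| Contrast | v | RR | SDLMI |
|---|---|---|---|
| End score adjusted for baseline | 0.8704 | 80.3% (79-82) | 81.4% (81-83) |
| End score only, or change if the SDs are of change | 1 | 74.7% (73-76) | 75.9% (75-78) |
| Change, single-time-point SDs, equal spread | 1.28 | 64.1% (62-66) | 65.3% (64-67) |

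In the last row the change contrast needs 1.28/0.8704 = 1.47 times the providers that the adjusted one does.

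**Step 3: unequal spread.** If the stated SD is the end SD and k = baseline SD/end SD, the variance factor for change is 1 + k² - 2rk.

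| k | Factor | RR | SDLMI |
|---|---|---|---|
| 0.36 | 0.870 | 80% | 81% |
| 0.50 | 0.890 | 79% | 81% |
| 0.75 | 1.02 | 74% | 75% |
| 1 | 1.28 | 64% | 65% |

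The factor is smallest at k = r = 0.36, where it equals 1 - r², and returns to 1 as k approaches 0. Change therefore never beats baseline adjustment.

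**The case against.** The strongest case on the other side has four parts.

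1. **The SD type is unstated.** A reader might infer that power is simply 64-65%. The article does not support that as an unconditional figure. It ties each SD to an effect in change, so an SD of change is a fair reading, and r could have been used earlier to derive that SD. Power is then about 73-78%. This stands, and both figures have to be quoted. Neither reaches 80% with a two-sided test.
2. **Equal spread is an assumption.** Fidelity is use of intervention components, so scores before training may sit near the floor with little spread. This also stands. But 80% is recovered only for a baseline SD of about half the end SD or less, and nothing in the article says that holds.
3. **The mixed model may already adjust for baseline.** A baseline-adjusted or common-baseline model fits the article's sentence, and the parameterisation may sit in an analysis plan not shown. So a reader cannot infer that an underpowered analysis will be run. What remains is that the article itself says the sizes power a comparison in change, and that stated contrast does not go with the stated numbers.
4. **The cure is small.** It is, but it corrects a stated power for the primary outcome and is more than a matter of wording.

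A reader might also take the match to 120 as reassurance about MTG. It is not, because 120 counts families.

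**Conclusion.** The point holds in a conditional form. The RR and SDLMI numbers belong to a baseline-adjusted comparison of end scores, while the text attaches them to a comparison in change. For that contrast, power is about 64% (RR) and 65% (SDLMI) with single-time-point SDs of equal spread, and about 73-76% and 75-78% with SDs of change. The listing of r as an input makes the single-time-point reading the more coherent one, but the article does not settle it.

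These figures assume a two-sided 5% test and the stated attrition and inflation factors. The conclusion covers RR and SDLMI only. It does not say that the planned numbers are too small: under baseline adjustment they deliver the stated 80%.

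**What to change.** - State whether 0.28 and 18.77 are SDs of a score (and at which time point) or of change.
- Define the primary contrast as end-of-intervention fidelity compared between arms with baseline fidelity as a covariate, or as a mixed model with a common baseline mean. Power at the planned sizes is then about 80% (RR) and 81% (SDLMI).
- Where no genuine pre-training fidelity score exists, compare end scores and restate power as about 75% (RR) and 76% (SDLMI).
- If the change contrast is kept, restate its power on the SD type declared.

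The cost is a sentence or two on the model and a restated power figure, with no added participants or data. The Trial status section says enrolment has begun, so this should be settled before outcome data are analysed.

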### Participants

We will recruit from underserved populations in urban, densely populated areas of 50,000 or more, and rural settings, areas that do not lie inside an urbanized area [37]. We will target autistic children but will include children with other neurodevelopmental disorders (NDD) at the request of the agency/school (see Table 1). MTG will include 48 Peer Navigators working at participating community agencies with peer navigator capacity (e.g. parent support centers; FQHC; community clinics; faith-based agencies) serving autistic children and children with NDD; and 240 families of children age 2–8 (with potential expansion based on community feedback) with ASD or NDD. RR will include 112 elementary school personnel (e.g., playground staff, classroom aides, teachers); and 152 autistic children and children with NDD ages 5–12 (4 per school). SDLMI will enroll 106 school staff serving autistic adolescents and adolescents with NDD; and 252 adolescents, ages 13- 19, who have ASD or NDD (6 per school).

**Table 1 Tab1:** Procedures & participants across concept studies of Evidence Based Interventions (EBIs)

	**UNITED**	**Implementation as Usual (IAU)**
Procedures across EBIs	Social network analysis to select implementers Collaborative Teaming Training Remote training & coaching in EBI EBI Implementation	Selection as usual of implementers (agency/school selects implementers) Remote training & coaching in EBI EBI Implementation
Mind the Gap (MTG)	10 community agencies 24 peer navigators 120 families with children 2–8 years 12 h of remote didactic training & up to 12 h remote supervision	10 community agencies 24 peer navigators 120 families with children 2–8 years 12 h of remote didactic training & up to 12 h remote supervision
Remaking Recess (RR)	19 schools 56 school personnel 76 autistic children 3 h of remote didactic training/12 h remote coaching RR implementation by practitioners	19 schools 56 school personnel 76 autistic children 3 h of remote didactic training/12 h remote coaching RR implementation by practitioners
Self-Determined Learning Model of Instruction (SDLMI)	21 schools 53 school personnel 126 autistic adolescents 2–4 h of remote didactic facilitator training/up to 12 h remote coaching SDLMI implementation by practitioners	21 schools 53 school personnel 126 autistic adolescents 2–4 h of remote didactic facilitator training/up to 12 h remote coaching SDLMI implementation by practitioners

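### The stated 80% power for MTG peer navigator fidelity cannot be reconciled with 24 navigators per arm; with one score per navigator it is about 17–23%

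*Protocol article*

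**What the plan says.** The Data analysis section says each of the three studies was sized on its primary outcome, the between-arm difference in change in implementation fidelity. Common to all three are a target power of 80%, a 5% type I error and a correlation of 0.36 between a provider's repeated fidelity measurements, taken from preliminary data. Dropout is an "estimated attrition rate of 20% for MTG and 30% for RR and SDLMI", and clustering enters as a "variance inflation factor (nesting of providers within schools/agencies) of 1.4 (RR) to 1.6 (MTG & SDLMI").

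The MTG target is a 15-point difference, which the article calls "a moderate standardized effect size of d = 0.48 in between strategies change in peer navigator fidelity"; the SD of 31 comes from earlier data. The effect is thus placed at the level of the navigator. The Fidelity section likewise makes the provider's fidelity the primary outcome.

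The Participants section gives the numbers: "MTG will include 48 Peer Navigators working at participating community agencies with peer navigator capacity", and 240 families. Table 1 shows each MTG arm as "10 community agencies 24 peer navigators 120 families with children". For comparison, each Remaking Recess (RR) arm has 56 school personnel and 76 children, and each Self-Determined Learning Model of Instruction (SDLMI) arm has 53 school personnel and 126 adolescents.

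**The concern.** The effect, the within-person correlation and the inflation factor are all described at provider level, yet 24 providers per arm is far too few to detect a standardized difference of 0.48 with 80% power, even before any loss for attrition or clustering. MTG is registered separately and has its own primary contrast. If its real power is well below 80%, a null result could be read as evidence that the UNITED strategy does not help peer navigation, when the target difference would usually have been missed. That would also bear on the article's aim of showing that UNITED generalises across three interventions.

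**Working it through.** **Inputs.** From Data analysis: 80% power; type I error 5% (sidedness not stated, two-sided assumed); r = 0.36; MTG difference 15, SD 31, d = 15/31 = 0.484; MTG attrition 20%; MTG VIF 1.6. From Table 1, per MTG arm: 10 agencies, 24 navigators, 120 families. Calculations use the two-sample t test.

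**1. Reproducing the stated 80%.** With baseline adjustment the SD is multiplied by √(1 − 0.36²) = 0.933. The n per arm before inflation is rounded up, multiplied by the VIF and divided by (1 − attrition).

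| Study | d | n before inflation | Inflated n per arm | Providers planned per arm | Families or youth planned per arm |
|---|---|---|---|---|---|
| RR | 0.2/0.28 = 0.714 | 28 | 28 × 1.4 / 0.7 = 56 | 56 | 76 |
| SDLMI | 15/18.77 = 0.799 | 23 | 23 × 1.6 / 0.7 = 52.6, so 53 | 53 | 126 |
| MTG | 0.484 | 60 | 60 × 1.6 / 0.8 = 120 | 24 | 120 |

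One formula returns the provider count for RR and SDLMI, and the family count for MTG. For MTG, other treatments of baseline give 138 per arm (r not used) or 174 (change score, variance factor 2(1 − r)). None gives 24.

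**2. Power with navigators as the unit, one score each.** Effective n = 24 × 0.8 / 1.6 = 12 per arm.

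| Analysis | SD factor | Power for 15 points | Difference detectable at 80% | Power with no attrition and no clustering (n = 24) |
|---|---|---|---|---|
| Change score | √(2 × 0.64) = 1.131 | 17% | 42.0 points | 31% |
| End of intervention only | 1 | 20.5% | 37.1 points | 38% |
| Baseline-adjusted | 0.933 | 23% | 34.6 points | 42% |

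If the SD of 31 is already the SD of change, the middle row applies.

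**3. Power with families as the unit.** There are 120/10 = 12 families per agency. A VIF of 1.6 then requires 1 + 11 × ICC = 1.6, so ICC = 0.055. Taken as the article describes it, on 24/10 = 2.4 navigators per agency, the same VIF requires 1 + 1.4 × ICC = 1.6, so ICC = 0.43. The article gives no ICC. Two assumed values, with baseline adjustment and 20% attrition:

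- ICC 0.10: VIF = 2.1, effective n = 96/2.1 = 45.7, power 69%.
- ICC 0.20: VIF = 3.2, effective n = 96/3.2 = 30, power 51%.

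**The case against.** **MTG was sized on families.** A reader might take this as established. The article does not say which count was used. The match for all three studies is strong circumstantial evidence, but it depends on the baseline-adjusted formula, and the article, which speaks of change, does not fix that formula. So the cause remains an inference. The mismatch with 24 navigators does not depend on it.

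**The true power is about 20%.** A reader might also infer this as a fixed fact. It holds for one score per navigator with the SD of 31 at navigator level, and the article states neither. The MTG fidelity section has 25% of sessions recorded and coded, and the analysis is a mixed model, so several scores per navigator may be available. If all 5 families per navigator completed the maximum of 12 sessions, 25% would be at most 15 coded sessions. Averaging 15 scores multiplies the variance by (1 + 14 × ICC)/15. Keeping the effective n of 12, end-only analysis and 22 degrees of freedom, power is about 27% at an assumed within-navigator ICC of 0.7, 49% at 0.3 and 81% at 0.1. The article gives no such ICC, so no single figure in that range can be prescribed.

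This objection limits how firmly a replacement figure can be stated, but it does not rescue the 80% claim as written. A session- or family-level analysis needs an inflation factor for clustering within navigators as well as agencies, and the 1.6 is described only for providers within sites. It also needs coded sessions, and the Limitations section says observer-rated instruments, fidelity among them, were replaced by self-ratings.

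The detailed random-effects structure is something an article may leave to the full protocol or analysis plan, and its absence is not part of this point.

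**Conclusion.** The concern holds as an inconsistency within the article: 80% power for a 15-point difference in navigator fidelity does not follow from the stated inputs with 24 navigators per arm. With one score per navigator and a two-sided 5% test, power is about 17–23% and the detectable difference about 35–42 points. Removing both attrition and clustering still leaves only 31–42%. If families were the intended unit, the 80% stands only for an ICC near 0.055 and falls to about 69% and 51% at assumed ICCs of 0.10 and 0.20.

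Confidence is high on the mismatch. It is only moderate on the explanation that families were counted in place of navigators, and on any replacement figure that uses several scores per navigator.

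**What to change.** 1. State the MTG unit of analysis for the primary outcome and the n that entered the power calculation.
2. Replace the 80% claim with the power and detectable difference for 48 navigators in 20 agencies. With one score per navigator these are about 17–23% for 15 points and 35–42 points at 80% power; name the treatment of baseline that goes with the figure chosen.
3. If several fidelity scores per navigator are to be analysed, first reconcile the MTG fidelity section (audio-coded sessions) with the Limitations section (self-rated fidelity). Then give the power under an inflation factor that covers clustering within both navigators and agencies, over a stated range of ICCs.

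This changes the sample-size statement only and needs no new participants. The cost is a less favourable stated power for MTG.

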## Trial status

All universities as well as each participating school district’s Institutional Review Boards have approved the study procedures. Each intervention is registered in clinical trials (MTG: NCT04972825; RR: NCT04972838; SDLMI: NCT04972851). At the time of submission of this manuscript (December, 2021), we have already enrolled participants (e.g., administrators, educators, providers) from community agencies and public elementary, middle, and high schools for data collection.

## Discussion

There are a growing number of EBIs for autistic individuals, but few are successfully implemented in under resourced communities and with historically marginalized and minoritized families [5, 8]. Conducting research in community-based settings creates opportunities to build capacity in existing service systems to ensure EBIs are readily accessible, relatively low-cost, and sustainable. In order to have a lasting impact, autism implementation research must focus on broadening access, expanding reach, and facilitating widespread availability of services in the community. Using effective implementation strategies is critical to support providers and organizations use EBIs. The proposed research activities will develop and simultaneously test a multifaceted implementation strategy to support the uptake and implementation of three EBIs that focus on early intervention, school-aged children, and adolescents with ASD with the goal of promoting access and services for underrepresented and under resourced communities. While all implementation strategies are designed to reduce the research-to-practice gap, most strategies are tested with one intervention and are not necessarily designed and tested to support implementation of multiple interventions concurrently. By applying this implementation strategy across our three EBIs, we increase the potential impact and generalizability of our findings. If beneficial, UNITED could be a much needed, “light touch” and low-cost implementation strategy to increase widespread use of EBIs in community settings. Additional research is needed to study the cost-effectiveness of UNITED in both high-resourced and low-resourced settings.

Each EBI has potential for high impact and research advancement. All three studies will be situated in schools or community agencies and will fully transfer the EBI and progress monitoring to the real-world team. Remote delivery of staff training has potential for expanding reach and increasing participation and engagement particularly during COVID-19 restrictions and social distancing requirements.

